#### Additional analyses including subgroup analyses

The primary subgroup analyses will be based on geographical region because demonstrating the consistency of any effect across multiple regions will improve the generalisability of the results [3]. The number of regions will depend on how clusters are distributed across states in India. Additional subgroup analyses will include age across the groups such as older adolescents (15–19 years), young adults (20–24 years), adults (25–59 years), and older adults (60 years and older) [50]; sex; the clinical cohorts blunt multisystem trauma, penetrating trauma, and severe isolated traumatic brain injury [51], and cluster size.

Models will also be extended to include an interaction between treatment and number of periods since first treated, to examine if there is any indication of a relationship between duration of exposure to the intervention and outcomes. This will allow us to consider different lag effects (i.e., it takes time for the intervention to become embedded within the culture before its impact can properly start to be realised); as well as weaning effects (i.e. the effect of the intervention starts to decrease – or fade). This type of analysis attempts to disentangle the effect of having differing lengths of exposure to the intervention.

### Methods in analysis to handle protocol non-adherence and any statistical methods to handle missing data {20c}

We will present the frequency and percentage of missing data for all variables. If the percentage of missing data for the primary outcome is less than 10%, we will perform a complete case analysis. If the percentage of missing data for the primary outcome is 10% or more, we will handle missing data depending on the missing data mechanism. If the data are missing at random (MAR), we will perform multiple imputation using multiple imputation by chained equations (MICE), imputing data for the primary outcome as well as all covariates included in the fully adjusted model. The number of imputations will be determined by the percentage of missing data, with a minimum of 20 imputations. If there is evidence that the data are missing not at random (MNAR), we will explore the impact of this assumption using a sensitivity analysis (e.g., pattern mixture models or selection models) to assess how robust our findings are to different assumptions about the missing data mechanism. Additionally, we will perform diagnostic checks after multiple imputation to ensure the quality of the imputation process, including comparing distributions of observed and imputed data and checking convergence.

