### Who will take informed consent? {26a}

Because this is a cluster randomised trial, with the intervention delivered to physicians, patient participants cannot consent to the intervention. Therefore, in this study, consent refers to consent for data collection.

Participants will be included in this trial with the following modes of consent:Opt-out consent for routinely recorded data and measurement of adherence to ATLS® principles. Consent for the collection of routinely recorded data, either through interviews or by extracting information from medical records, as well as for the measurement of adherence to ATLS® principles, will be presumed unless explicitly declined. This approach is justified because the trial is considered to pose minimal risk and because data collection will be noninvasive. Additionally, obtaining consent specifically for the measurement of adherence to ATLS® principles could interfere with the provision of care and cause undue stress for patients and their representatives. Participants, or their legally authorised representatives, will be provided with written information about the study upon their arrival at the hospital.Opt-in consent and assent for nonroutinely recorded data. Informed consent for nonroutinely recorded data will be actively sought from participants or their legally authorised representative. For participants who are between 15 and 18 years of age, we will obtain both the assent of the participant as well as the consent of their guardian or legally authorised representative. Participants and their representatives will be approached after admission. Consent and assent will be written for participants who are admitted to the hospital and verbal for participants who are transferred or discharged before the clinical research coordinators have had an opportunity to approach them. Verbal consent will be audio recorded.Waiver of informed consent for participants who are unconscious or otherwise unable to provide consent and who do not have a legally authorised representative. This group represents the most severely injured participants, who must be included to make the trial representative of the entire population of trauma participants. Participants who regain consciousness will be informed about the study and asked to consent to the collection of nonroutinely recorded data.

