### Plans to promote participant retention and complete follow-up {18b}

The primary outcome is extracted from medical records and is known to be missing to a negligible extent. To promote complete telephone follow-up following discharge, we collect multiple phone numbers for each participant. For outcomes collected through telephone follow-up, at least three calls are attempted. Depending on the response, a subsequent call to complete the follow-up may be scheduled. In cases where no contact can be established despite repeated attempts, the participant is classified as lost to follow-up.

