## Statistical methods

### Statistical methods for primary and secondary outcomes {20a}

The primary analysis set will include all observations within clusters with available data and irrespective of the receipt of the intervention. Clusters and observations within clusters will be considered exposed to the intervention after the date at which the cluster was scheduled for transition. All the data will be included except the transition phases.

We will not adjust for multiplicity of analyses because none of the secondary outcomes will be singularly more important. However, all secondary outcomes will be interpreted with due consideration for the way all are affected by the intervention without undue emphasis on a single outcome that might be statistically significant when all others appear to have remained unchanged.

We have several requirements for the analysis model. First, all analyses will consider the clustered nature of the design. Second, as the trial has only 30 clusters, it will be essential for the model to allow for correction due to the small number of clusters. Third, as the design is a stepped-wedge study, we will adjust for temporal confounding following standard approaches with categorical effects for the period of the study (1 month) [47, 48].

In the case of binary outcomes, the primary estimand will be the odds ratio obtained from a mixed effects binomial regression with a logit link. We will also apply a binomial model with an identity link to estimate the risk difference. These models will be fitted using residual pseudo-likelihood estimation based on linearisation with subject-specific expansion (RSPL). If the binomial model with the identity link does not converge then only an odds ratio will be reported.

We will include fixed effects for period and a fixed effect for intervention exposure. The primary analysis will allow for clustering as a random cluster and random cluster by period effect. To correct potential inflation of the type I error rate due to the small number of clusters, a correction for a small number of clusters will be applied. Our primary method will be a Kenward-Roger correction [49], but this choice might be updated based on new methods work available closer to the end of patient inclusion, and may differ for the outcomes collected via the complete main stepped-wedge design and incomplete nested staircase designs.

We will use a two-sided significance level of 5% and estimate 95% confidence intervals.

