### Methods for additional analyses (e.g. subgroup analyses) {20b}

#### Sensitivity analyses

We will conduct a sensitivity analysis to explore whether models with more complicated correlation structures are better fits to the data. These models are not our primary analysis models as there is limited understanding of when such models will converge and how to choose between the various correlation structures that may be plausible. To this end, we will additionally fit generalised linear mixed models (with the same link functions and fixed effects described above) to include a discrete time decay correlation structure that includes a random cluster effect with an auto-regressive structure (AR [1]).

To explore whether the fixed period effect is both parsimonious and adequate for representing the extent of any underlying secular trend, we will model the time effect using a spline function. Models will also be extended to include random cluster by intervention effects (with a non-zero covariance term) to examine whether the results are sensitive to the assumption of no intervention by cluster interaction. A fully adjusted covariate analysis will adjust for a set of prespecified individual-level covariates of known prognostic importance.

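### Imputation of covariates in the fully adjusted analysis is triggered by missing primary outcomes, which the plan expects to be negligible, so that sensitivity analysis is complete-case however incomplete its covariates are

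*Protocol article*

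**What the plan says.** Four places in the protocol article bear on this.

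- **Missing data, section {20c}.** One quantity, the percentage of missing primary outcomes, selects the method. Below the threshold: "If the percentage of missing data for the primary outcome is less than 10%, we will perform a complete case analysis". Above it: "If the percentage of missing data for the primary outcome is 10% or more, we will handle missing data depending on the missing data mechanism". Within that second branch, and only under missing at random, multiple imputation by chained equations is planned, "imputing data for the primary outcome as well as all covariates included in the fully adjusted model".
- **Retention and follow-up, section {18b}.** "The primary outcome is extracted from medical records and is known to be missing to a negligible extent".
- **Sensitivity analyses, under {20b}.** "A fully adjusted covariate analysis will adjust for a set of prespecified individual-level covariates of known prognostic importance".
- **Statistical methods, section {20a}.** The analysis set is broad: "The primary analysis set will include all observations within clusters with available data and irrespective of the receipt of the intervention". The primary model needs no patient-level covariates: "We will include fixed effects for period and a fixed effect for intervention exposure".

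No other section of the article gives a rule for missing covariates.

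**The concern.** The plan recognises that the fully adjusted model may need its covariates imputed, but it ties that step to the completeness of a different variable. Whether age, injury severity or admission physiology (examples only, since the article does not list the covariates) needs imputing depends on how complete those variables are. Here it depends on how complete the mortality record is. With outcomes nearly complete, the imputation branch is not reached, even if a large share of patients lacks at least one covariate.

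What is at stake is the comparison between the adjusted and the primary result. If the adjusted model runs on fewer patients, a difference between the two mixes the effect of adjustment with the effect of dropping patients, and precision is lost. Who is dropped also matters. On patients unable to consent and without a representative, section {26a} says: "This group represents the most severely injured participants, who must be included to make the trial representative of the entire population of trauma participants". A complete-case adjusted model could lose some of the severely injured again if their records are less complete.

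**Working it through.** **1. Trace the rule.** The input is the percentage of missing primary outcomes. Section {18b} expects it to be negligible, so it falls below 10% and section {20c} gives a complete-case analysis. Covariate missingness does not enter the decision: with 0% of outcomes missing, the rule returns the same answer for covariates that are 1% or 40% missing. The fully adjusted model then uses only patients with every covariate recorded. The primary model, with period and intervention as its fixed effects, loses nobody for this reason.

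**2. Reference sample size.** Section {14} plans at least 4320 patients. This is reproduced by 30 clusters × 12 analysed months (13 less the 1-month transition phase) × 12 patients per month = 4320.

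**3. Possible loss of patients (assumed inputs).** With k covariates, each missing with probability m independently, the share dropped is 1 − (1 − m)^k. Dropped share, with patients left of 4320:

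| Covariates | m = 2% | m = 5% | m = 10% |
|---|---|---|---|
| 3 | 5.9% (4066) | 14.3% (3704) | 27.1% (3149) |
| 5 | 9.6% (3905) | 22.6% (3343) | 41.0% (2551) |
| 8 | 14.9% (3675) | 33.7% (2866) | 57.0% (1860) |

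For example, 1 − 0.95^5 = 1 − 0.7738 = 22.6%. Independence is not conservative in the reassuring direction: if all five gaps always fell in the same patients, only 5% would be lost (4320 × 0.95 = 4104 left).

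**4. Possible effect on the estimate (assumed completeness).** The plan's mortality figures are 20% under standard care and 15% after training. The crude odds ratio is (0.15/0.85)/(0.20/0.80) = 0.706 and the risk difference is −5.0 points. Let r_d and r_s be the share with complete covariates among deaths and survivors. Then:

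- complete-case risk = p·r_d / [p·r_d + (1 − p)·r_s]
- complete-case odds ratio = 0.706 × (r_d/r_s in intervention) / (r_d/r_s in standard care)

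*Completeness depends on death only* (80% of deaths, 95% of survivors, both conditions):

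- standard care: 0.16/(0.16 + 0.76) = 17.4%
- intervention: 0.12/(0.12 + 0.8075) = 12.9%
- risk difference −4.45 points instead of −5.0; odds ratio still 0.706, because the two completeness ratios cancel.

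*Completeness depends on death and on condition, but with the same ratio* (deaths 80% then 84%, survivors 90% then 94.5%): 0.84/0.945 = 0.80/0.90 = 0.889, so the odds ratio is again 0.706. Dependence on both outcome and exposure is therefore not enough to bias it.

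*The ratio differs between conditions* (deaths 80% complete in standard care and 90% in intervention; survivors 95% in both):

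- standard care 17.4%; intervention 0.135/(0.135 + 0.8075) = 14.3%
- odds ratio 0.706 × (0.90/0.95)/(0.80/0.95) = 0.706 × 1.125 = 0.794; risk difference −3.1 points
- overall loss is small: 0.20 × 0.20 + 0.80 × 0.05 = 8.0% in standard care, and 0.15 × 0.10 + 0.85 × 0.05 = 5.75% in intervention.

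These are crude two-by-two figures. They show direction and rough scale, and are not the covariate-adjusted mixed-model odds ratio.

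**The case against.** **The reading is partly inferred.** The threshold sentence speaks of missing primary outcomes and nowhere says that covariates will not be imputed. It could be a rule about the outcome that is silent on covariates. Section {17a} promises a full analysis plan describing all sensitivity analyses before the trial statistician receives data, and covariate handling is often left to such a plan. This has some weight. But covariate imputation is written into the triggered procedure, so the natural reading is that it does not happen otherwise. An analysis plan that imputed covariates at low outcome missingness would depart from the stated rule, and one that followed the rule would inherit the problem.

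**The scope is narrow.** This stands in full. One of several sensitivity analyses is affected. The article does not designate it as the check on case mix, and section {21b} separately compares patient characteristics between conditions at the interim analysis.

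**Selective loss of deaths is not documented.** A reader might infer that patients who die would be dropped more often, since section {10} includes deaths before admission and Table 2 places much of the data collection during assessment and hospital care. A reader might also infer that training in a structured survey would make records more complete. Neither is stated. Section {18a} says source data are reviewed for all in-hospital deaths, section {19} plans ongoing review of missing data, and section {26a} allows routine data to come from interviews as well as records. If the covariates are as simple as age and sex, the loss could be trivial.

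**Imputation is not a complete cure.** If covariates are absent because of unrecorded severity, imputation under missing at random need not remove the bias. Section {20c} already promises missingness percentages for all variables, so a large overall loss would be visible, though no breakdown by condition or vital status is promised.

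**Conclusion.** The point holds as a mis-specified trigger. On the plan's own expectation of nearly complete outcomes, the fully adjusted sensitivity analysis is complete-case regardless of covariate missingness, and may rest on a smaller, selected subset of the primary analysis patients.

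Its size cannot be taken from the article. With five covariates each 5% missing, the loss is about 23% under independence and as little as 5% if the gaps coincide. Across the wider assumed grid it runs from 6% to 57% under independence.

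Three stronger conclusions are not supported:

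- that the primary result is at risk: its model has no individual-level covariates;
- that deaths will be dropped disproportionately, or that completeness will rise after training: both are assumptions;
- that the odds ratio, the primary estimand for binary outcomes, is biased simply because selection depends on outcome and exposure: the death-to-survivor completeness ratio must differ between conditions. Loss by death alone would shift a risk difference, if one is reported for this model, and leave the crude odds ratio as it was.

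It is worth correcting because the repair is cheap.

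**What to change.** In section {20c}, separate the two triggers. Keep the 10% rule for the primary outcome and add, for example: *For the fully adjusted analysis, missing covariates will be multiply imputed regardless of the percentage of missing primary outcomes. The imputation model will include the primary outcome, intervention exposure, period and cluster, so that the adjusted and primary analyses use the same patients.* Also commit to reporting covariate completeness by condition and by vital status, which shows directly whether the completeness ratio differs between standard care and intervention.

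The cost is one or two sentences and some computing time. Chained-equation imputation with at least 20 imputations is already planned, and no new data are needed. Section {17a} promises the analysis plan before the trial statistician receives data, so the change can be made before results are seen. The downside is that the adjusted result then rests on a missing-at-random assumption for the covariates, which should be stated alongside it.

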#### Patient participants

The inclusion criteria for the patient are as follows:At least 15 years of age;Trauma occurring less than 48 h before arrival at the hospital;Presenting to the emergency department of the participating hospitals, with a history of trauma defined as any of the reasons listed in the International Classification of Diseases chapter 20 as the reason for presenting;Admitted, or died between arrival at the hospital and admission, or were referred/transferred from the emergency department of a participating hospital to another hospital for admission; andManaged by a participating unit in the emergency department.

The exclusion criteria for the patient participants are as follows:Presenting with isolated closed extremity fracture;Admitted directly to a ward without being seen by a physician in the emergency department.

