### Intervention description {11a}

The intervention in this study is the ATLS® training, which is a proprietary 2-day course that teaches a standardised approach to trauma patient care using the concepts of a primary and secondary survey. The programme was developed by the Committee of Trauma of the American College of Surgeons. The course includes initial treatment and resuscitation, triage and interfacility transfers. Learning is based on practical scenario-driven skill stations and lectures and includes a final performance proficiency evaluation [13].

We will train physicians who initially resuscitate and provide trauma care during the first hour after patient arrival at the emergency department. These physicians can be casualty medical officers, surgical residents, or emergency medicine residents, depending on the setup at each participating centre. Physicians will be trained in an accredited ATLS® training facility in India. Training occurs during the transition phase in each cluster. Our experience from the pilot study is that study sites adhere to the training slot allotted to them through the trial [31]; therefore, we judge the risk of clusters implementing ATLS® before their randomised implementation sequence to be very low.

We will train the number of units of physicians needed to reach the required patient sample size. We estimate that this will require training an average of ten physicians per hospital, which should mean that we can train one to two units per hospital on average. This is possible because many hospitals in India organise physician staffing of their emergency departments in units, and physicians in the same unit work together in the emergency department on the same days of the week. These physicians’ duties may change into another department as per the residency programme. Therefore, we will collect data only on the days when these units work. The units selected from each hospital will be a convenience sample of all eligible units in those hospitals. We will also assess adherence to ATLS® principles before and after implementing ATLS® training.

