### Strategies to improve adherence to interventions {11c}

Adherence to ATLS® is one of the secondary outcomes and will be monitored using a checklist that covers the key steps of the ATLS® primary survey (see Table 1), for patients included using the nested staircase design. We will not enforce adherence to ATLS®, as this study is of real-world effectiveness of ATLS® rather than efficacy.

**Table 1 Tab1:** Primary and secondary outcomes

Outcome	Source of data	Mode of collection
Primary outcome		
In-hospital mortality within 30 days of arrival at the emergency department	Patient hospital records. If the patient has been transferred to another hospital, the clinical research coordinators will collect data on this outcome by calling the patient or the patient’s representative, or by contacting the hospital to which the patient was transferred. Data on this outcome will be collected continuously during the trial	Main stepped-wedge design. Collected for all patients
Secondary outcome		
All-cause mortality within 24 h, 30 days and 3 months after arrival at the emergency department	Patient hospital records or telephone follow up. If the patient has been transferred to another hospital or discharged, the clinical research coordinators will collect data on this outcome by calling the patient or a patient representative, or by contacting the hospital to which the patient was transferred. Data on this outcome will be collected continuously during the trial	Main stepped-wedge design. Collected for all patients
Length of emergency department stay	Data on this outcome will be collected from patient hospital records	Main stepped-wedge design. Collected for all patients
Length of hospital stay	Data on this outcome will be collected from patient hospital records	Main stepped-wedge design. Collected for all patients
Intensive care unit admission	Data on this outcome will be collected from patient hospital records	Main stepped-wedge design. Collected for all patients
Length of intensive care unit stay	Data on this outcome will be collected from patient hospital records	Main stepped-wedge design. Collected for all patients
Return to work at 30 days and 3 months after arrival at the emergency department	Data on this outcome will be collected in person if the patient is still in hospital, or by phone if the patient has been discharged	Main stepped-wedge design. Collected for all patients

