## Outcomes {12}

The primary outcome will be in-hospital mortality within 30 days of arrival at the emergency department. There are several secondary outcomes (see Table 1). Outcomes that cannot be confirmed at the designated time point will be considered missing.

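### Below 10% missing primary outcomes the plan prescribes complete-case analysis alone, and it makes the missing-not-at-random analysis depend on evidence that observed data cannot give

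*Protocol article*

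**What the plan says.** Section 20c of the protocol article sets a switch on one percentage for the whole trial. Below it: "If the percentage of missing data for the primary outcome is less than 10%, we will perform a complete case analysis". Above it: "If the percentage of missing data for the primary outcome is 10% or more, we will handle missing data depending on the missing data mechanism", with multiple imputation by chained equations if the data are missing at random. The only analysis aimed at informative missingness comes next and has its own condition: "If there is evidence that the data are missing not at random (MNAR), we will explore the impact of this assumption using a sensitivity analysis". The sensitivity analyses in section 20b concern correlation structure, the shape of the time effect, a random intervention effect and covariate adjustment. None concerns missing outcomes.

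Section 18b gives the expected extent: "The primary outcome is extracted from medical records and is known to be missing to a negligible extent". It gives no figure. Three other places bear on that statement:

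- The patient eligibility criteria include those who "were referred/transferred from the emergency department of a participating hospital to another hospital for admission".
- Table 1 (in section 11c) describes another source for them: "If the patient has been transferred to another hospital, the clinical research coordinators will collect data on this outcome by calling the patient" or a representative, or by contacting the receiving hospital.
- Section 12 adds: "Outcomes that cannot be confirmed at the designated time point will be considered missing".

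Section 11a describes the training: "The course includes initial treatment and resuscitation, triage and interfacility transfers".

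**The concern.** The reason given for negligible missingness, extraction from records, does not cover transferred patients. Their outcome has to be traced outside the participating hospital and is set to missing if tracing fails. Because the training covers transfer decisions, the number and severity of transferred patients could shift between phases. Coordinators who trace outcomes also know the phase, since section 17a leaves outcome assessors unblinded. A single overall percentage cannot show a difference between phases.

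The MNAR condition does not help. Whether unobserved deaths are more frequent than observed ones, given what was measured, cannot be learned from the observed data. An analysis that waits for such evidence may never be triggered, even if its sentence is read as applying at any percentage. On the more natural reading it applies only at 10% or more. What is at stake is a primary result that depends on untested assumptions about the missing patients, with no planned analysis in this document to show how much it depends on them.

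**Working it through.** **Inputs from the protocol article.** Mortality of 20% under standard care and 15% after training, 30 clusters, about 12 observations per cluster-month and at least 4320 patients (section 14); 13 months per cluster, one of them a transition month (section 8) that is not analysed (section 20a). The primary estimand is the odds ratio (section 20a).

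**The plan's own figures.** 30 × 12 × 12 = 4320, as stated. The target is a risk difference of 5.0 points, or an odds ratio of (0.15/0.85)/(0.20/0.80) = 0.706.

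**What the threshold admits.** 10% of 4320 is 432, so up to 431 missing outcomes still lead to complete case only. With half the patients in each phase, the 5-point effect is 2160 × 0.05 = 108 deaths, about a quarter of 431.

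**Formula.** With true risk p, missing share m and risk among the missing q, the complete-case risk in a phase is (p − m·q)/(1 − m). All values of m and q below are assumptions, since the documents give none. Overall percentages assume equal numbers in each phase.

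**Cases where little happens (q twice the phase risk)**

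- 5% missing in each phase: (0.20 − 0.05×0.40)/0.95 = 18.9% and (0.15 − 0.05×0.30)/0.95 = 14.2%. The difference is 4.7 points and the odds ratio 0.709.
- 0% against 2% missing (1% overall): 20.0% and (0.15 − 0.02×0.30)/0.98 = 14.7%. The difference is 5.3 points and the odds ratio 0.689.

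**Differential missingness below 10% overall (standard care first)**

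| Missing | Risk among missing | Complete-case risks | Difference | Shift from 5.0 |
|---|---|---|---|---|
| 4% / 14% | 40% / 30% (twice phase risk) | 19.2% / 12.6% | 6.6 | +1.6 |
| 4% / 14% | 40% / 40% | 19.2% / 10.9% | 8.2 | +3.2 |
| 6% / 12% | 40% / 30% | 18.7% / 13.0% | 5.8 | +0.8 |
| 6% / 12% | 40% / 40% | 18.7% / 11.6% | 7.1 | +2.1 |
| 9% / 9% | 35% / 15% | 18.5% / 15.0% | 3.5 | −1.5 |

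Row 1 in full: (0.20 − 0.04×0.40)/0.96 = 0.1917 and (0.15 − 0.14×0.30)/0.86 = 0.1256. On the primary scale this is an odds ratio of 0.606 against the true 0.706. Row 2 differs only in its second term: (0.15 − 0.14×0.40)/0.86 = 0.1093.

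**No true effect.** With 20% mortality in both phases, 4% against 14% missing and q = 40%, the risks are 19.2% and (0.20 − 0.14×0.40)/0.86 = 16.7%. That is an apparent benefit of 2.4 points (odds ratio 0.85).

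**Assumption-free bounds.** If an observed difference of −5 points comes with a share m missing in each phase, the full-data difference lies within −5(1 − m) ± 100m points. The upper end reaches zero at m = 0.05/1.05 = 4.8%. These bounds are extreme (all of the missing die in one phase and none in the other). They show only that a threshold of 10% does not by itself guarantee a robust conclusion.

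**The case against.** The case against has several parts, and much of it stands.

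- **Extent.** Section 18b says missingness is negligible, and nothing in the document contradicts the extent. At about 1% there is no practical problem.
- **Mechanism.** A reader might infer that transfers cause the missingness and that training changes transfers. Neither is stated. No transfer share or tracing rate is given, and removal of data at a participant's request (section 15) is another source.
- **Severity of the scenarios.** If transfers were the only source and half of those patients were lost, 4% against 14% would need the transfer share to rise from 8% to 28%; if a third were lost, from 12% to 42%. Holding mortality among the missing at 40% in both phases also raises their relative risk from 2.0 to 2.67. Hence the lower figure of 1.6 points.
- **Unequal shares alone do not bias.** Missingness must also be related to death within phase. Where measured severity explains that relation, the adjusted analysis in section 20b gives some protection.
- **Other safeguards.** The interim analysis (section 21b) looks for substantial missing outcome data and for differential ascertainment between conditions. Section 18b provides for several telephone numbers and at least three call attempts.
- **The analysis plan.** Section 17a promises a plan describing all sensitivity analyses, which is not at hand and may add one.

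These points limit the size of the concern. They do not remove it, because the point is about a rule that the article states and not about missing detail. The interim look is tied to feasibility and monitoring and not to any analysis of the effect. An analysis plan that followed section 20c as written would need nothing more below 10%.

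**Conclusion.** The rule is weak in two respects: complete case is the only prescribed handling below 10% overall, and the MNAR analysis waits for evidence that cannot be had. The reassurance in section 18b rests on a reason that does not cover transferred patients. The consequence is conditional. It is trivial at about 1% missing, or with similar missingness and similar relative risk among the missing in both phases. It is about 1.6 to 3.2 points against a 5-point target under an assumed 4% against 14% missing.

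A reader might infer that a bias close to the target effect is to be expected, or that complete case must be replaced by multilevel imputation as the primary analysis. The documents support neither: they give no rates by phase, and they state that missingness is negligible. What they support is that the plan should show how far the result depends on the missing patients, whatever their share.

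**What to change.** 1. Report the number and percentage of missing primary outcomes by phase and by transfer status.
2. Whatever the percentage, accompany the primary analysis with a delta-adjusted sensitivity analysis. It should vary mortality among the missing separately in the standard care and intervention phases and give the tipping point at which the conclusion changes.
3. Delete the condition that there be evidence of MNAR.

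Complete case may remain the default primary analysis below the threshold. The cost is a change of wording and one extra analysis, which will be uninformative if missingness is truly negligible. Section 17a has the analysis plan published before the trial statistician receives any data, so the change can be made there without looking data-driven.
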